**Fig. 1 Fig1:**
[figure not shown]
Summary of intervention future health today implementation trial

Sites will be offered a software education session and provided with training videos (Supplemental appendix 1). Practices will also be provided a CKD education session (Supplemental appendix 2) and ongoing support by a nephrologist and nephrology nurse practitioner as required. During the trial practices will be encouraged to use the cohort function and complete quality improvement activities, commencing with screening patients at risk and providing a diagnosis to those with biochemical signs of CKD. Trial staff will assist practices by creating these initial cohorts.

Sites will be asked to nominate a practice champion. Practice champions will be a point of contact for the duration of the trial and asked to promote use of FHT at their practice site. They will also be providing survey and interview feedback at the end of year one and three, in addition to at least one primary care physician at the practice (Supplemental appendix 3–5).

Primary care data will be linked with tertiary centre records at baseline and then 6 monthly to end of the trial. Analysis of the retrospective cohort will be undertaken at baseline, with interim analyses yearly to end of trial. Yearly interim analysis will enable any program issues to be identified and addressed and identify areas where primary care practices may require further support. Evaluation of usability, feasibility and satisfaction will be undertaken at the end of year one and at the end of the trial.

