### Outcomes

Primary outcome: change in the number of patients who are meeting quality of care indicators in three domains:

Screening: an appropriately timed kidney health check in patients at risk of kidney disease.Diagnosis: total number of patients with coded diagnosis of CKD.Management: patients with CKD on a renin angiotensin system inhibitors with at least 12 months follow up following a CKD diagnosis.

Secondary outcomes: these are divided into patient centric, health centric and overall evaluation.

Patient centric secondary outcomes:

1.1 Change in number of patients achieving the kidney cycle of care. This involves monitoring of renal function, albuminuria, diabetes (if diabetic), fasting lipids and blood pressure measurement.1.2 Change in proportion of patients on any antiproteinuric medication including angiotensin converting enzyme inhibitor (ACE inhibitor) or angiotensin receptor blocker (ARB), sodium glucose co-transporter 2 inhibitor (SGLT2 inhibitor) and mineralocorticoid antagonists (MRA). With sub analysis of each medication class.1.3 Change in proportion of patients with type two diabetes and CKD prescribed an SGLT2 inhibitor.1.4 Change in urinary albumin to creatinine ratio (uACR) in patients with CKD diagnosis and at least 12 months follow up.1.5 Change in slope of estimated glomerular filtration rate (eGFR) in patients with a coded diagnosis of CKD compared 2 years prior and 2 years post and adjusted for baseline function. The index date will be CKD diagnosis coded or if CKD already diagnosed at entry into study.1.6 Subgroup analysis: Subgroup analysis will be undertaken comparing those with a coded diagnosis of CKD, to those with measured CKD (all patients meeting CKD diagnostic criteria) and possible CKD (patients who have one eGFR or uACR in diagnostic criteria). This will be conducted as CKD is well known to be under coded in the medical health record. CKD will be defined according to the Kidney Disease Improving Global Outcomes criteria [13].1.7 Potential further subgroup analysis will be conducted with frequent, moderate, and minimal users of FHT (if a difference is found between practices).

Health centric secondary outcomes:

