### Data collection and management

Three years of historical primary practice data will be collected (historical control) and compared with three years of active intervention. Primary practice data will be extracted from the primary care electronic medical record and FHT database in a non-re-identifiable format using software Grhanite™ [14]. Grhanite™ software enables data linkage without needing re-identification of patient data [14]. FHT usage will be extracted from the FHT monitoring system. Hospital utilisation, including admission and outpatient attendance to relevant specialties will be extracted from the hospital electronic record system. Hospital data will be converted to a non-re-identifiable format using Grhanite™ prior to being provided to the research team and then subsequently linked to the primary care data. All data will be housed on a secure server. Survey data will be collected using REDCap electronic survey and data capture tools hosted by Western Health [15, 16]. REDCap is a secure web-based software platform designed to support data capture for research studies [15, 16]. Practice interviews will be recorded and transcribed using a voice-to-text function, and then manually checked for accuracy.

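### Outcome 1.5 splits the eGFR slope at a coding date that can itself depend on low eGFR, so for newly coded patients the before/after contrast is biased, with a sign that depends on coding delay

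*Protocol article*

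**What the plan says.** Protocol article, Outcomes, item 1.5 defines the change in eGFR slope "in patients with a coded diagnosis of CKD compared 2 years prior and 2 years post and adjusted for baseline function". It then sets the split point: "The index date will be CKD diagnosis coded or if CKD already diagnosed at entry into study". There are therefore two branches: the coding date for newly coded patients, and study entry for those who already carry the diagnosis.

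The Intervention section describes how new codes arise. Practices do quality improvement work, "commencing with screening patients at risk and providing a diagnosis to those with biochemical signs of CKD", and "Trial staff will assist practices by creating these initial cohorts". Item 1.6 states that "CKD will be defined according to the Kidney Disease Improving Global Outcomes criteria" and that "CKD is well known to be under coded in the medical health record".

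Data collection and management sets the time frame: "Three years of historical primary practice data will be collected (historical control) and compared with three years of active intervention". No parallel control is described for item 1.5.

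**The concern.** A slope comparison around a date is sound only if the date was not chosen by looking at the outcome. Here, for a patient coded because of eGFR, the qualifying low results come just before the code. They contain real decline plus downward noise. If they fall at the end of the prior window they make the prior slope too steep. The post slope is unaffected, so the patient seems to improve.

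There are two further difficulties. For newly coded patients the contrast is before versus after coding, not before versus after FHT, although the Discussion justifies the design by an interruption at the intervention. Time after FHT start but before coding counts as prior. In addition, three active years leave little room for two years of follow-up after a code entered late.

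Item 1.5 is the only outcome on the course of kidney function. An artefact there could be read as slowed disease progression when wider roll-out is considered.

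**Working it through.** The protocol article gives no expected slope, eGFR variability or testing interval, so there is no figure of its own to reproduce. The check has two parts.

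**1. Slope artefact with no intervention effect**

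From the protocol: two-year windows either side of the index, and an index at coding.

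Assumed: starting eGFR mean 75 (SD 12); slope mean -1 per year (SD 1.5); visit-to-visit noise SD 3 to 5; tests every 3 or 6 months; qualification at the second consecutive value below 60; 200,000 simulated patients per setting. The prior window includes the value at the index date and the post window leaves it out. The artefact is the mean of (post slope minus prior slope), each fitted by least squares. The true artefact is zero.

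Coding at qualification (mL/min/1.73m2 per year):

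| Noise SD | Test interval | True slope of those selected | Prior | Post | Artefact |
|---|---|---|---|---|---|
| 3 | 3 months | -2.32 | -3.33 | -2.32 | +1.01 |
| 3 | 6 months | -2.33 | -3.67 | -2.33 | +1.33 |
| 5 | 3 months | -2.19 | -4.36 | -2.16 | +2.20 |
| 5 | 6 months | -2.19 | -5.04 | -2.19 | +2.85 |

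The post slope recovers the true slope of the selected patients; the error is in the prior slope.

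Effect of a delay between qualifying and being coded (noise SD 5, six-monthly tests; a separate run, hence +2.78 rather than +2.85 at zero delay):

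| Delay (years) | Prior | Post | Artefact |
|---|---|---|---|
| 0 | -5.02 | -2.24 | +2.78 |
| 0.5 | -3.84 | -2.13 | +1.71 |
| 1.0 | -2.74 | -2.17 | +0.57 |
| 1.5 | +0.21 | -2.19 | -2.41 |
| 2.0 | -0.76 | -2.16 | -1.40 |
| 2.5 | -2.14 | -2.19 | -0.05 |

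The sign reverses because the low qualifying values move from the end of the prior window to its start, where they flatten the slope. From 2.5 years they lie outside the window. Across noise SD 3 to 5 and both test intervals, the artefact is about +1.0 to +2.9 at zero delay, +0.4 to +0.6 at 1 year, -0.3 to -2.5 at 1.5 to 2 years, and about zero from 2.5 years.

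Two comparisons show that the index rule is the cause:

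- With a fixed calendar index, as for patients already diagnosed, the prior and post slopes are -1.00 and -0.99 against a true -1.
- Splitting at FHT start and using only values after the qualifying result gives an artefact of about zero.

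**2. Window arithmetic**

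Data run from year -3 to year +3 around FHT start. Two full prior years need an index at or after -3 + 2 = -1. Two full post years need an index at or before 3 - 2 = +1. Among patients coded in the active period, only those coded in year 1 can have two full years afterwards.

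- Uniform coding: (3 - 2)/3 = 33%.
- Coding that declines exponentially at rate r per year: (1 - e^-r)/(1 - e^-3r), which is 51% at r = 0.5, 67% at r = 1 and 79% at r = 1.5.
- A practice that starts 6 months late against a fixed end date, with uniform coding: (1 - 0.5)/(3 - 0.5) = 20%.

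**The case against.** The strongest reply is that the mechanism applies to only part of the analysed group and does not always flatter FHT. Most of this stands.

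- **Unaffected patients.** Those already diagnosed are indexed at study entry, a date not chosen by eGFR. Diagnoses that rest on uACR alone do not carry the mechanism either. Both groups dilute any bias.
- **Backlog.** The protocol itself says that CKD is under-coded, and the roll-out begins with prepared cohorts. Many patients may be coded long after they first qualified, where the artefact shrinks, reverses or disappears. A reader might infer that 1.5 is bound to show a false slowing. The documents do not support that, because the distribution of delays is unknown.
- **Windows.** A reader might infer that most patients coded under FHT would be excluded. The text does not require complete windows, whereas item 1.4 does state a minimum: "Change in urinary albumin to creatinine ratio (uACR) in patients with CKD diagnosis and at least 12 months follow up". How to treat partial windows may properly be left to an analysis plan. The figure of 67% without two full years holds only for uniform coding, and the initial cohorts make early coding plausible.
- **Baseline adjustment.** The term baseline function is not defined. If it means eGFR at the index date, it is a selected value and also an end point of the prior slope, so adjusting for it would not be a safe remedy. It could mean something else, and this was reasoned rather than simulated.
- **Known limitation.** The Discussion concedes that a pre-post design cannot show causation. That concession concerns background trends; it does not cover a bias created by the index rule.

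What does not fall away is that, for patients coded on eGFR, the split point depends on the outcome. An error whose sign turns on coding delay is no reassurance when FHT is intended to change that delay.

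**Conclusion.** The point holds in a limited form. For newly coded patients whose diagnosis rests on eGFR, item 1.5 as fixed gives a biased slope contrast without any intervention effect. The bias can be as large as or larger than the assumed mean decline of 1 mL/min/1.73m2 per year, in the false-slowing direction when coding is prompt and in the opposite direction at delays of 1.5 to 2 years. The net bias over the mixed population cannot be determined from the protocol article.

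The magnitudes rest on the assumed eGFR course, noise, testing interval and qualification rule; the dependence on the index date does not. It is also certain that this branch does not estimate a before/after FHT contrast, and that two full post-index years require coding in active year 1. This is one secondary outcome and the primary outcomes are untouched, but the rule should be corrected.

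**What to change.** Make the main analysis of 1.5 a change in eGFR slope at each practice's FHT start date:

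- **Population:** patients who met the measured-CKD criteria of item 1.6 before that date.
- **Data:** only eGFR values after the qualifying result, with all available follow-up, whether or not it reaches two years on either side.
- **Model:** a linear mixed model with patient random intercept and slope, a practice effect, and a slope change at FHT start. Do not adjust for eGFR measured at the index date.
- **Coding-date contrast:** keep it, if wanted, as descriptive only.

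The cost is analysis wording and programming; the data are already to be extracted. The downside is real: patients who first qualify after FHT start, including those found through FHT screening, do not contribute to the slope-change estimate, and prior slopes are shorter for those who qualified late in the historical period.

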**Methods:**

This pre-post implementation trial using an interrupted time series design will evaluate the clinical and service outcomes of Future Health Today, using a mixed methods study in twenty general practices with an estimated population size of 150,000. Deidentified patient data will be extracted from participating practices to examine the primary aims of the study. Surveys and semi-structured interviews with general practice will inform secondary hypotheses. Data linkage between primary care and tertiary care data will examine the broader health service impacts.

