### Study population

This study will take place in twenty general practices in western Melbourne and will be supported by the local tertiary hospital. This is an area with high burden of chronic disease.

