### Data analysis

Descriptive statistics will be used to describe the baseline characteristics in the historical control and active group. Primary end points will be calculated, and a chi square test will be used to assess if the difference between pre and post-test is significant for the primary outcomes (nominal data), with *p* < 0.05 considered significant.

Univariate analysis will be undertaken for each of the outcomes to compare differences in the characteristics of the historical control versus the three year active intervention. For continuous variables, the data will be tested for normality using Shapiro Wilk test and equality of variances using Levene’s test. If these assumptions hold true, parametric tests like the t-test or ANOVA will be used. If these assumptions do not hold then nonparametric alternatives will be considered. For categorical variables a Chi Squared test will be used. When comparing multiple groups, post hoc investigations may be included with Bonferroni corrections. Regression models will be used to control for co-variates.

The analysis will be undertaken 3 years prior to study commencement (historical control) and then interim analysis yearly until trial conclusion.

Survey responses will be analysed to understand the usability of FHT software and if practice staff felt the software aided their management of CKD. Semi structured interviews of practice champions and additional primary care physicians will be conducted via zoom or phone, according to interviewees preference. Interview transcripts will be coded by at least two researchers. The clinical performance feedback intervention theory framework will be used for the overall implementation evaluation combining survey and interview data [12].

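### Outcome 1.7 groups recorded FHT use into three classes across 20 practices; if it is run, modelling use as a continuous practice-level measure would keep power that the cut gives away

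*Protocol article*

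**What the plan says.** In the protocol article, Outcomes, item 1.7 is listed under the patient-centred secondary outcomes and worded as a possible addition: "subgroup analysis will be conducted with frequent, moderate, and minimal users of FHT (if a difference is found between practices". No measure of use, class limits, test or unit is given for it.

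The surrounding text supplies four relevant facts:

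- **Data collection and management:** "FHT usage will be extracted from the FHT monitoring system". Use is therefore collected as data, whatever is later done with it.
- **Study population:** "This study will take place in twenty general practices in western Melbourne". The abstract adds the size, "twenty general practices with an estimated population size of 150,000".
- **Data analysis, comparisons:** for continuous variables that meet the assumptions, "parametric tests like the t-test or ANOVA will be used"; categorical variables get a chi-square test. Then: "When comparing multiple groups, post hoc investigations may be included with Bonferroni corrections".
- **Data analysis, regression:** "Regression models will be used to control for co-variates". Regression on use as a graded exposure is not mentioned.

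**The concern.** Cutting a graded measure into three classes treats every practice within a class as having the same use. If the classes are then compared by a general three-group test, their order is ignored as well, and two degrees of freedom go on a question (does the effect rise with use?) that needs one. With 20 practices there is little information to spare: near-equal classes hold 7, 6 and 7.

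The trial has no concurrent control, and the Discussion accepts that causation cannot be assessed directly. A gradient of improvement with use would be one supporting sign that change is linked to the software. An analysis that misses a real gradient more often than it need do weakens that sign. The answer would also depend on where the class limits are set.

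**Working it through.** **Inputs from the protocol article.** 20 practices; about 150,000 patients, so 150,000 / 20 = 7,500 per practice; three classes of use; p below 0.05 "considered significant" (stated for the primary outcomes, taken here as two-sided).

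**Inputs assumed, because the protocol gives none.** One summary change per practice; effect linear in use; use spread normally or uniformly across practices; class sizes 7/6/7 unless stated. The protocol gives no power or effect size for 1.7, so there is no stated figure to reproduce.

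**Tests compared.**
- Linear term in use: t = r√18 / √(1 − r²) on 18 df, where r is the sample correlation of use with effect.
- Three-group ANOVA: F on 2 and 17 df.
- Ordered trend: the same t, with use replaced by scores 0, 1, 2.

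**Step 1: what the cut alone discards.** For uniform use in equal thirds, the variance within a third is (1/3)² = 1/9 of the total, so the class means keep 8/9, or 89%. For normal use, the outer-third means lie at ±0.3636 / (1/3) = ±1.091 SD, so the classes keep (2/3) × 1.091² = 0.79. An ordered test loses only this 11% to 21%. An unordered test also pays for the second degree of freedom.

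**Step 2: power by strength of gradient** (simulation, 20 practices, normal use, 7/6/7; true correlation in the first column):

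| Correlation | Linear term | ANOVA | Loss (points) |
|---|---|---|---|
| 0.3 | 25% | 15% | 10 |
| 0.4 | 44% | 25% | 19 |
| 0.5 | 65% | 39% | 26 |
| 0.6 | 84% | 58% | 26 |
| 0.7 | 96% | 78% | 18 |

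With no gradient, both reject about 5% of the time. The ordered trend on the same classes loses 8 to 13 points for correlations of 0.4 to 0.7. Bonferroni pairwise tests (any of three significant) give 22%, 36%, 55% and 76% at 0.4 to 0.7, and somewhat less if each pair uses only its own variance, so they do not recover the loss. A rank correlation gives 57%, 77% and 91% at 0.5, 0.6 and 0.7.

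**Step 3: fix the linear term at 80% power and vary the setting.**
- ANOVA, 7/6/7: uniform 59.4% (80 − 59.4 = 20.6 points lost); normal 53.4% (26.6 lost).
- ANOVA, 5/10/5: uniform 56.1% (23.9 lost); normal 54.9% (25.1 lost).
- Ordered trend over these settings: 68.1% to 73.4% (6.6 to 11.9 lost).

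**Step 4: range as the linear term's power goes from 50% to 90%,** which lies inside the 44% to 96% that Step 2 gives for correlations of 0.4 to 0.7.
- ANOVA: 17 to 24 points (uniform, all splits tried); 20 to 27 (normal, 7/6/7 or 5/10/5), up to 30 with unequal classes.
- Ordered trend: about 5 to 11 (uniform) or 8 to 14 (normal).

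**Step 5: skewed use.** With lognormal use and an effect linear in raw use, the loss runs from about 10 to over 60 points. If the effect follows log use instead, a three-group trend test is about as powerful as a linear term in raw use. The scale on which use is entered therefore matters.

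**The case against.** A reader might infer that the plan commits to an unordered ANOVA with Bonferroni follow-up on 20 practice values, and so loses some 17 to 25 points whatever the circumstances. The document does not support that:

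- Item 1.7 is optional and depends on a difference between practices being found.
- The class labels are ordered by their meaning, and no test is named for them. An ordered trend is not excluded.
- The tests in Data analysis are introduced for the historical control against the active period, and the Bonferroni step is permissive. Neither is tied to 1.7.
- The unit is inferred. The reference to practices in 1.7 suggests practice-level classes, but users could mean clinicians. A patient-level chi-square over about 150,000 people would not show the power of a 20-unit test; whether it allowed for clustering is a separate matter.
- The Discussion gives the task of separating the intervention from natural change to the interrupted time series. That 1.7 should test a rising effect is a reading of its purpose, not a statement in the protocol.
- Details of a possible subgroup analysis are commonly left to the analysis plan, which is not shown.

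Most of this stands, and it limits the size and weight of the point. It does not remove it. The three-way cut is a stated choice rather than an omitted detail, and the graded data are already to be collected. If practices are the exposure unit, there are at most 20 distinct values of use however many patients are counted. Even the ordered test loses some power under roughly normal or uniform use.

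**Conclusion.** The point holds as a conditional and minor one. If use is classified by practice, with a roughly normal or uniform spread and a linear gradient of moderate to strong size (correlation about 0.4 to 0.7), the cut costs about 17 to 27 points of power with a three-group ANOVA, which is the multi-group test that Data analysis names. It costs about 5 to 14 points with an ordered trend on the same groups. At a correlation of 0.3 the ANOVA loss is about 10 points. Step 3 shows that more than half of the ANOVA loss comes from ignoring the order of the classes rather than from the cut itself.

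The effect size, spread of use, class sizes, test and unit are all assumptions, so no single figure can be attributed to the protocol. Because 1.7 is exploratory and optional, no main conclusion of the trial depends on it. It is a cheap improvement.

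**What to change.** State that, if 1.7 is carried out, its main analysis takes FHT use as a continuous practice-level variable, for example log uses per 1,000 patients per month. Enter it as an interaction with the intervention term, with practice as the unit of analysis or as the cluster. Add a rank correlation as a check that does not rely on normality. Keep the frequent, moderate and minimal groups as a descriptive display only. Fix the measure and its scale before usage results are seen.

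The cost is a few sentences in the analysis plan; usage is already to be extracted, so no new data are needed. The small downside is that a monotone shape is assumed, so a plateau at high use would be seen only in the descriptive display.
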